### 6.1.8. Interim analysis

A single interim analysis of the primary efficacy endpoint will be conducted after the first 200 subjects have completed the 6-week double-blind treatment period. Treatment arms determined to have minimal possibility of efficacy in a futility analysis will be dropped from the study. In addition, an estimate of variance of the primary endpoint will be performed and an evaluation of effect of SNAP will be assessed. Because the study will not be terminated due to any premature treatment efficacy, there should NOT be a penalty on the global Type I error rate for this interim look.

For the interim analysis, the standard deviation of the changes of the pain score will be estimated to see if the assumed standard deviation of 0.35 is valid. Next, a “predicted” 95% confidence interval for the treatment difference between each dose and placebo groups will be computed for the primary efficacy endpoint. If the confidence interval for a dose group does not include 0.17 (projected placebo effect, see Section 6.3 for justification), this dose group will be dropped from the study. However, this treatment effect of 0.17 will be re-estimated from the interim analysis data, and the decision rule can be modified based on the new estimate. If subjects with a negative SNAP do not benefit from the treatment, future subjects with a negative SNAP will not be enrolled in the study. Finally, the sample size based on the new estimate of the standard deviation will be determined so that the length of the 0.95 confidence intervals of the difference of changes between a dose group and the placebo will be within 0.24 (twice of 0.12, see Section 6.3 Sample size and power considerations) at the final analysis.

The interim analysis will be performed by CBAR at the Harvard School of Public Health. The results will be shared only with members of the independent Data Safety Monitoring Board (DSMB), who will make recommendations to the Protocol Chair and the study team regarding protocol modifications. In order to avoid bias, the DSMB will not disclose any findings except for issuing a decision statement. All staff, including the Savient clinical team and investigators, involved in the conduct of the study will remain blinded to the results of such analyses.

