## Sample size and power considerations

Based on two studies of neuropathic pain in subjects with HIV-SN20, 21, the average placebo response in the Gracely pain scale is about 0.17, and the standard deviation of the change in Gracely pain scale is approximately 0.35. Therefore, any treatment differences of less than 0.17 can be considered to be not clinically meaningful. This study is designed to detect a minimum treatment difference of 0.17 between any dose group and placebo. In order to have at least 80% power to detect this difference and a significance level of 0.05 (2-sided), 70 evaluable subjects at the end of the trial in the 4 mg, 8 mg, 16 mg and placebo groups are required. The power to detect this difference between the 2 mg and placebo groups will also be calculated before the final efficacy analysis. With 70 subjects per group, the 95% confidence interval for the changes between any dose group and the placebo covers (d-0.12, d+0.12), where d is the observed difference between the two groups. Allowing for early dropouts and assuming the enrollment of 45 subjects in the 2 mg group, 355 subjects will need to be enrolled for the final analysis.

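### The futility margin of 0.17 is called both a placebo effect and a treatment effect, and may be re-estimated from unblinded interim data without saying which quantity is meant or how the drop rule changes

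*Protocol*

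**What the plan says.** Section 6.3 (Sample size and power considerations) reports from two earlier studies that "the average placebo response in the Gracely pain scale is about 0.17" and that "the standard deviation of the change in Gracely pain scale is approximately 0.35". The next sentence draws a conclusion about a different quantity: "Therefore, any treatment differences of less than 0.17 can be considered to be not clinically meaningful". The design effect then takes the same value: "This study is designed to detect a minimum treatment difference of 0.17 between any dose group and placebo".

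Section 6.1.8 (Interim analysis) applies this number after 200 subjects complete six weeks. A predicted 95% confidence interval for each dose-minus-placebo difference is compared with 0.17, described there as the projected placebo effect with a pointer to Section 6.3. A dose whose interval does not contain 0.17 is dropped. The following sentence renames the number and opens the rule: "this treatment effect of 0.17 will be re-estimated from the interim analysis data, and the decision rule can be modified based on the new estimate".

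Section 3.3.3 makes the interim analysis the stated exception to keeping the treatment codes unbroken. Section 6.1.8 has it run by an independent statistical centre, with results going only to the DSMB.

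**The concern.** One number plays three roles: the mean change on placebo, the smallest difference between arms worth having, and the margin for dropping a dose. A within-arm placebo change does not by itself set a between-arm difference, so the inference in Section 6.3 does not follow.

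The double label matters once the number may be re-estimated, because the result depends on which quantity is meant:

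- **Placebo response.** This is how Section 6.3 introduces 0.17 and how Section 6.1.8 first labels it. The margin then rises with the interim placebo mean, and the same mean is subtracted from every dose. A chance high value in one shared arm counts twice against all doses.
- **A dose's own observed difference.** An interval centred on that value always contains it, so that dose can never be dropped.
- **An effect pooled over doses.** This avoids the circularity, but the protocol does not mention it.

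At stake is the primary objective in Section 6.1, which is to find at least one dose better than placebo. An effective dose could be removed by a rule that was altered after unblinded data were seen.

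**Working it through.** **1. The plan's own figures.** Inputs from Section 6.3: difference 0.17, SD 0.35, two-sided 0.05, power at least 80%.

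- n per group = 2 × (1.96 + 0.84)² × 0.35² / 0.17² ≈ 67 (68 with the t-test).
- Power at 70 per group is 82.0% (81.4% with the t-test), consistent with "70 evaluable subjects at the end of the trial in the 4 mg, 8 mg, 16 mg and placebo groups are required".
- Half-width at 70 per group = 1.96 × 0.35 × √(2/70) = 0.116, stated as 0.12.

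The sample size is sound. The issue is the interim rule.

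**2. Assumptions for the interim.**

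- 200 completers give 200/5 = 40 per arm (five arms) to 200/4 = 50 per arm (four arms).
- SE of a difference = 0.35 × √(2/n) = 0.078 (n = 40) or 0.070 (n = 50).
- The protocol does not define the predicted interval, so two half-widths h are used: interim width (0.153 or 0.137) and final width (0.116).
- A dose is dropped only if its upper limit lies below the margin.
- The true difference is 0.17.

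**3. Margin fixed at 0.17.** P(drop) = Φ(−h/SE).

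- Interim width: Φ(−1.96) = 2.5%.
- Final width: Φ(−0.116/0.078) = 7% (n = 40); Φ(−0.116/0.070) = 5% (n = 50).

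The true placebo response does not enter.

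**4. Margin set to the interim placebo mean.** Let A and P be the interim dose and placebo means and π the true placebo response. The dose is dropped if (A − P) + h < P, that is, if A − 2P < −h. The mean of A − 2P is 0.17 − π. Its SE is 0.35 × √(5/n) = 0.124 (n = 40) or 0.111 (n = 50). So P(drop) = Φ((π − 0.17 − h)/SE).

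| True placebo response π | Interim width, n = 40 / 50 | Final width, n = 40 / 50 | Range |
|---|---|---|---|
| 0.17 (Section 6.3) | 10.8% / 10.8% | 17.4% / 14.7% | 11-18% |
| 0.25 (assumed) | 27.7% / 30.3% | 38.6% / 37.3% | 28-39% |
| 0.30 (assumed) | 42.5% / 47.4% | 54.5% / 55.1% | 42-55% |

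Simulation agrees. Chance alone moves this margin: with 40 placebo subjects the SE of the placebo mean is 0.35/√40 = 0.055, so a true 0.17 gives 0.17 ± 1.96 × 0.055, or about 0.06 to 0.28.

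**5. Final power.** This was simulated with 70 per arm at the end, counting a dose as successful if it is not dropped and is significant.

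- No dropping: 82%.
- Margin fixed at 0.17, upper limit only: 80-82%.
- Margin set to the placebo mean, π = 0.17: about 74-79%.

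**6. The exclusion wording.** Read literally, the rule also drops a dose whose whole interval lies above 0.17. With the margin fixed and this two-sided wording, a true 0.17 dose is dropped 5-14% of the time (twice the step 3 figures) and power is about 73-79%. A dose with a true difference of 0.30 is dropped for being too good 38-58% of the time. Fixing the margin alone therefore does not restore 80%.

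**The case against.** The strongest reply is that the protocol permits a modification and does not order that the margin become the placebo mean; the sentence itself speaks of a treatment effect. That stands: the drop rates in step 4 describe one reading. It does not clear the text, because the other label, and the derivation in Section 6.3, point to the placebo response.

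A reader might infer that re-estimation fails however it is read. That goes too far, since a pooled effect would work. It is simply not what the protocol states.

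A reader might also take the 39% and 55% drop rates as the expected harm. The documents give no placebo response other than about 0.17, so those figures illustrate sensitivity only. Nor does a drop rate equal a loss of power: at a placebo response of 0.17, 57-75% of the doses dropped would have missed significance at the end anyway. The larger falls in power, to 44-67%, occur only at the assumed responses of 0.25 and 0.30.

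Requiring a drug to add at least as much as placebo does is a possible clinical benchmark. It is a judgement, though, and Section 6.3 presents it as a deduction.

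The safeguards are real. The analysis is independent, only the DSMB sees results and it makes recommendations, dropping an arm needs an amendment (Sections 3.1.3 and 4.1), and there is no stop for efficacy. They limit operational bias and answer a Type I error charge, which is not made here. They do not correct the criterion the DSMB is handed. Doses sharing a placebo arm tend to fail together under a fixed margin too; the moving margin strengthens this (correlation 0.8 against 0.5).

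**Conclusion.** The point holds as a defect in what the protocol states, not as detail left to an analysis plan. The margin carries two incompatible labels, its derivation does not follow, and the rule may be rewritten from unblinded data without a named quantity, formula or limit.

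Under the placebo reading and the assumptions in step 2, the cost at the documented placebo response is moderate: 11-18% of fully effective doses dropped against 2.5-7%, and power of about 74-79% against the stated 80%. The documents do not support saying that the rule must remove effective doses, or that power collapses at the planned placebo response. The two-sided exclusion wording is a separate fault of similar size and needs correcting at the same time.

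**What to change.** - **Section 6.1.8:** delete the re-estimation sentence. State that the futility margin is the design treatment difference of 0.17, fixed before the interim, and remove its description as a placebo effect.
- **Section 6.1.8:** replace the test of whether the interval contains 0.17 with a one-sided rule: drop a dose only if the upper limit of its interval is below 0.17.
- **Section 6.3:** give 0.17 as the design difference in its own right, separate from the placebo response, and remove the inference from one to the other.
- Keep the interim re-estimation of the SD, for sample size only.
- Bring the monitoring plan into line.

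These are wording changes and need no new data. The cost is that the margin can no longer be moved at the interim. With the corrected rule, a dose with a true difference of 0.17 is dropped 2.5-7% of the time whatever the placebo response, and final power stays at 80-82%.

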## 6.2. Safety monitoring and periodic safety reporting

A periodic safety report will be provided to the Data Safety Monitoring Board and external personnel once every 6 months without breaking the blind, as detailed in the Monitoring Plan developed by CBAR. The report will include summary tables of the safety parameters listed in Section 6.1.6. If there are any safety concerns, the committee will request the trial statistician to perform additional analyses by treatment. Further, summary information on Serious Adverse Events will be provided to the DSMB, DAIDS and the study team as they occur.

## Sample size and power considerations

Based on two studies of neuropathic pain in subjects with HIV-SN20, 21, the average placebo response in the Gracely pain scale is about 0.17, and the standard deviation of the change in Gracely pain scale is approximately 0.35. Therefore, any treatment differences of less than 0.17 can be considered to be not clinically meaningful. This study is designed to detect a minimum treatment difference of 0.17 between any dose group and placebo. In order to have at least 80% power to detect this difference and a significance level of 0.05 (2-sided), 70 evaluable subjects at the end of the trial in the 4 mg, 8 mg, 16 mg and placebo groups are required. The power to detect this difference between the 2 mg and placebo groups will also be calculated before the final efficacy analysis. With 70 subjects per group, the 95% confidence interval for the changes between any dose group and the placebo covers (d-0.12, d+0.12), where d is the observed difference between the two groups. Allowing for early dropouts and assuming the enrollment of 45 subjects in the 2 mg group, 355 subjects will need to be enrolled for the final analysis.

# 7. Notable laboratory value criteria, special methods and scales

## 7.1. Criteria for clinically notable laboratory abnormalities

Safety laboratories for this study will include serum chemistry, hematology and liver function tests. Urinalysis will also be performed along with safety laboratories (see Appendix 6). Due to the advanced state of immunodeficiency and multiple concomitant medications anticipated for subjects in this study, a greater variability in laboratory tests is anticipated than would be seen in a normal adult population. In addition, it is anticipated that most subjects will have multiple other concomitant conditions that may adversely influence laboratory tests. Therefore, **determination of causality for laboratory abnormalities will be particularly difficult and will require active, ongoing clinical correlation on the part of the investigator**. The central laboratory will report the predetermined clinically notable laboratory results as specified below to the investigative site immediately. The investigator is responsible for evaluating the laboratory abnormality as a potential adverse event, and for determining required follow-up. Source records should clearly document all follow-up performed.

For the purposes of this study, **clinically notable serum chemistry** abnormalities will include blood urea nitrogen (BUN) >3 times the upper limit of normal (ULN), creatinine >3 times ULN, SGOT or SGPT >5 times ULN. Since values of total bilirubin are influenced by concomitant medications, a total bilirubin of >5 times ULN will be considered clinically notable. **Clinically notable hematology** values will include a hemoglobin of <6.9 g/dL, a total white blood cell count of <2 x 109/L or  27.75 x 109/L, and a platelet count of <50 x 109/L or 1000 x 109/L.

## Special methods and scales

Anti-prosaptide antibody will be measured at Visit 7 via an ELISA assay. Details regarding collection and shipment of samples are given in the investigator folder supplied to each site. Results from the prosaptide antibody tests and prosaptide drug levels will remain blinded to investigators as well as all NARC and Savient study personnel until after the database lock and unblinding of the database at the conclusion of the study.

Further information is provided under Appendix 2, Section 2.2-AP2.

# Appendix 1: Ethics and good clinical practice

This study must be carried out in compliance with the protocol and in accordance with the sponsor’s (Savient) standard operating procedures. These are designed to ensure adherence to Good Clinical Practice, as described in:

1. ICH Harmonized Tripartite Guidelines for Good Clinical Practice 1996. Directive 91/507/EEC, The Rules Governing Medicinal Products in the European Community.
2. US 21 Code of Federal Regulations dealing with clinical studies (including parts 50 and 56 concerning informed consent and IRB regulations).
3. Declaration of Helsinki, concerning medical research in humans (Recommendations Guiding Physicians in Biomedical Research Involving Human Subjects, Helsinki 1964, amended Tokyo 1975, Venice 1983, Hong Kong 1989, Somerset West 1996).

The investigator agrees, when signing the protocol, to adhere to the instructions and procedures described in it and thereby to adhere to the principles of Good Clinical Practice that it conforms to. Copies of these regulations are available at:

[www.fda.gov/cder/guidance/959fnl.pdf](http://www.fda.gov/cder/guidance/959fnl.pdf)

[www.access.gpo.gov/nara/cfr/waisidx_00/21cfr50_00.html](http://www.access.gpo.gov/nara/crf/waisidx_00/21cfr50_00.html)

[www.access.gpo.gov/nara/cfr/waisidx_00/21cfr56_00.html](http://www.access.gpo.gov/nara/cfr/waisidx_00/21cfr56_00.html)

[www.fda.gov/oc/health/helsinki89.html](http://www.fda.gov/oc/health/helsinki89.html)

## 1.1-AP1. Institutional review board/Independent ethics committee

Before implementing this study and initiating any protocol-related activities, the protocol, the proposed informed consent form and other information to subjects must be reviewed by a properly constituted Institutional review board/Independent ethics committee (IRB/IEC). The original copy of the signed and dated statement that the protocol and informed consent have been approved by the IRB/IEC must be sent to sponsor’s representative (PPD) before study initiation. The investigator must maintain a copy of the approval letter that contains the study number, protocol title, and identification of all documents approved. The name and occupation of the chairman and the members of the IRB/IEC must also be supplied to PPD. If the investigator or any member of the study staff is also a member of the IRB/IEC, he or she must provide a written statement that he/she absented from voting on this study. Any amendments to the protocol, other than administrative ones, must also be approved by the IRB/IEC.

The investigator must submit annual status reports to the IRB/IEC and provide a copy to PPD. Within three months after completion or termination of the study a final report must be submitted to the IRB/IEC and PPD. The investigator must maintain an accurate and complete record of all submissions made to the IRB including a list of all reports and documents submitted.

The IRB will comply with all federal, state, and local laws. The investigator will obtain from the IRB/ERC and submit to PPD a signed statement indicating that it complies with Good Clinical Practices. A sample IRB compliance letter is provided in the investigator folder at each site.

The sponsor (Savient) and the sponsor’s representative (PPD) will promptly be advised of any regulatory inspection (relating to this study) of either the institution or the IRB. The investigator will promptly provide a copy of any inspection report.

## 1.2-AP1. Informed consent (IC)

The investigator must explain to each subject or subject’s legally authorized representative the nature of the study, its purpose, the procedures involved, the expected duration, the potential risks and benefits involved and any discomfort it may entail. Each subject or subject’s legally authorized representative must be informed that participation in the study is voluntary and that he/she may withdraw from the study at any time and that withdrawal of consent will not affect his/her subsequent medical treatment or relationship with the treating physician.

This informed consent should be given by means of a standard statement, written in non-technical language. The subject should read and consider the statement before signing and dating it, and should be given a copy of the signed document. No subject can enter the study before informed consent has been obtained.

The study specific informed consent form must be submitted by the investigator with the protocol for IRB/IEC approval. The sponsor supplies a proposed informed consent form, which complies with regulatory requirements and is considered appropriate for the study. Any changes to the proposed consent form suggested by the investigator must be agreed to by Savient, and a copy of the approved version must be provided to the PPD monitor after IRB/IEC approval.

A copy of the FDA regulations with regard to informed consent, the World Medical Association Declaration of Helsinki, and a sample consent form are available at:

[www.access.gpo.gov/nara/cfr/waisidx_00/21cfr50_00.html](http://www.access.gpo.gov/nara/crf/waisidx_00/21cfr50_00.html)

[www.fda.gov/oc/health/helsinki89.html](http://www.fda.gov/oc/health/helsinki89.html)

## 1.3-AP1. Compliance with law, audit, and debarment

By signing this protocol, the investigator agrees to conduct the study in an efficient and diligent manner and in conformance with this protocol; generally accepted standards of Good Clinical Practice; and all applicable federal, state, and local laws, rules and regulations relating to the conduct of the clinical study.

The investigator also agrees to allow monitoring, audits, Institutional review board/Independent ethics committee review and regulatory agency inspection of study-related documents and procedures and provide for direct access to all study-related source data and documents.

The investigator agrees not to seek reimbursement from subjects, their insurance providers, or from government programs for procedures included as part of the study reimbursed to the investigator by Savient.

The investigator shall prepare and maintain complete and accurate study documentation in compliance with Good Clinical Practice standards and applicable federal, state, and local laws, rules and regulations. For each subject participating in the study, the investigator shall provide all data and submit any other reports to PPD as required by this protocol or by any other agreement with Savient.

Study documentation (see Document retention section) will be promptly and fully disclosed to PPD and Savient by the investigator upon request and also shall be made available at the investigator’s site upon request for inspection, copying, review and audit at reasonable times by representatives of Savient or any regulatory agencies. The investigator agrees to promptly take any reasonable steps that are requested by Savient as a result of an audit to cure deficiencies in the study documentation and CRFs.

Persons debarred from conducting or working on clinical studies by any court or regulatory agency will NOT be allowed to conduct or work on Savient studies. The investigator will immediately disclose in writing to Savient if any person who is involved in conducting the study is debarred, or if any proceeding for debarment is pending or, to the best of the investigator’s knowledge, threatened.

## 1.4-AP1. Compliance with financial disclosure requirements

By signing this protocol, the investigator agrees to provide to Savient accurate financial information to allow submission of complete and accurate certification and disclosure statements as required by US Food and Drug Administration regulations (21 CFR Part 54). This requirement also extends to sub-investigators.

